#### Program engagement

Program engagement will be measured by automatic data collection on number of assignments accessed, tasks completed. Association between program engagement metrics and treatment outcomes will be explored.

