#### Treatment as usual (TAU)

The GPs design a treatment plan based on current routines for treating alcohol problems at the PC clinic. The fact that all participants are offered contact with a GP enables participants in need of specialized care of any kind to be referred by the GP. All GPs are offered a brief training in giving feedback on the assessment and biomarkers and the use of medication for treatment of alcohol dependence. Together this serves as the base of TAU which is provided to the participants in both study arms.

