#### Baseline and follow-up assessments

Questionnaires: Time Line Follow Back 30 days [﻿20﻿] is used to assess mean weekly alcohol consumption and heavy-drinking days. Severity of hazardous drinking and dependence is assessed with the Alcohol Use Disorders Identification Test (AUDIT) [22] and the *ICD-10* criteria for alcohol dependence (The World Health Organization, 1992). Symptoms of anxiety and depression are assessed with the Hospital Anxiety and Depression Scale (HADS) [22]. The EuroQol five dimensions, five levels health survey (EQ-5D-5 L) questionnaire measure health-related quality of life [23]. Satisfaction with treatment is assessed, only at 12 weeks’ follow up, with the Client Satisfaction Questionnaire (CSQ) [24].

Biomarkers: blood is analyzed for standard biomarkers of heavy drinking and liver pathology at each assessment; levels of phosphatidylethanol (PEth); gamma-glutamyl transferase (GGT); aspartate amino transferase (AST) and alanine amino transferase (ALT).

Biological specimens will not be stored as a part of the study. Results from blood samples are provided via the patient file system at the PC clinics and blood samples are destroyed after analysis.

Patients will be contacted by automatically created messages in the web-based treatment platform and by the research nurse when necessary during weeks 13 and 52 in order to conduct the follow-up assessments and blood tests. At week 13 the Client Satisfaction Questionnaire (CSQ) is added. Assessment completeness is checked automatically on the treatment platform and if not completed participants cannot proceed to the next step. Participants will be contacted by the research nurse and reminded if assessments are not completed using a combination of messages from the treatment platform, phone calls, emails and text messaging in order to improve retention in treatment and prevent loss to follow-up over the follow-up period. The research nurse will also remind the participants to leave the blood tests during weeks 13 and 52 and collect the results from the patient files.

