### Statistical analyses and sample size calculations

Baseline participant characteristics stratified by treatment group will be presented. Group differences will be tested using a *t* test for continuous variables and chi-square tests for categorical outcomes. Multiple imputation will be used to replace missing internal values where appropriate. Within-group changes in the primary outcome (alcohol consumption) and secondary outcomes (*ICD-10* criteria, AUDIT scores, depression, anxiety, EQ-5D-5 L and biomarkers) at 12 and 52 weeks will be analyzed according to the intention-to-treat principle, using linear mixed models and Poisson regression where appropriate. The models will further be adjusted for baseline covariates and treatment adherence. Per-protocol analyses will also be presented. All tests will be two-sided and *p* values of less than 0.05 considered statistically significant.

The study is designed to demonstrate statistical superiority. An effect-size of 0.61 has been shown in previous Internet studies on high consumers in the general population [25]. Due to a lack of studies on alcohol-dependent patients, our estimate is based on a more conservative effect-size of 0.4, which requires the estimated sample size of 100 participants in each arm to get a power of 80% and a statistically significance 0.05 when using a *t* test. Given an estimated dropout in iCBT of 30%, 260 participants are included in the study [26].

No interim analyses are planned.

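### The treatment-receipt data described cover iCBT only, so per-protocol and adherence-adjusted analyses built on them would be one-sided, and TAU received is not described as recorded in either arm

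*Protocol article*

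**What the plan says.** **Receipt of iCBT.** Under Program engagement: "Program engagement will be measured by automatic data collection on number of assignments accessed, tasks completed". The stated use is exploratory: "Association between program engagement metrics and treatment outcomes will be explored".

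**Receipt of TAU.** Under Treatment as usual (TAU), the content is left to the GP: "The GPs design a treatment plan based on current routines for treating alcohol problems at the PC clinic". Both arms receive it: "Together this serves as the base of TAU which is provided to the participants in both study arms". Baseline and follow-up assessments lists a 30-day drinking diary, AUDIT, ICD-10 criteria, HADS, EQ-5D-5L, a satisfaction questionnaire at week 13 and four blood markers. None of these records whether the GP visit took place, how many contacts followed or whether medication was prescribed. The research nurse will, however, go to the clinic records at weeks 13 and 52 to "collect the results from the patient files".

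**Blinding.** Randomization, treatment allocation and blinding says that participants and the research nurse know the allocation. It does not say whether GPs do.

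**Analyses.** Under Statistical analyses and sample size calculations, outcomes "will be analyzed according to the intention-to-treat principle, using linear mixed models and Poisson regression where appropriate". The article then adds two analyses that need adherence data: "The models will further be adjusted for baseline covariates and treatment adherence" and "Per-protocol analyses will also be presented". It defines neither adherence nor the per-protocol set.

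**The concern.** Two of the planned analyses depend on adherence, and the only adherence data described exist in one arm. With those data, poor adherers can be removed from the iCBT group but not from the TAU-only group. People who complete online assignments may well be better motivated and drink less later whatever the programme does. A per-protocol comparison built this way would then favour iCBT through selection alone.

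The adherence adjustment has the same root. Adherence arises after randomisation and, as described, has no value for a TAU-only participant. Once it is in the model, the arm coefficient no longer estimates the randomised effect.

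A separate and milder issue is interpretation. The hypothesis concerns iCBT added to TAU. TAU is at GP discretion and participants know their allocation, so GP attendance or prescribing could come to differ by arm. The listed data would not show this, and part of any difference might then come from TAU rather than from the programme.

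**Working it through.** **1. The plan's own figure, used here only as a yardstick.** Effect size 0.4, 80% power, two-sided 0.05: n per arm = 2 × (1.96 + 0.842)² / 0.4² = 2 × 7.85 / 0.16 = 98.1, so 99. The exact t test gives 99.1, so 100 per arm is reproduced. Nothing below depends on it.

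**2. What the described data allow.**

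| | iCBT + TAU | TAU only |
|---|---|---|
| Programme use | logged automatically | does not exist |
| GP visit, contacts, medication | not described as recorded | not described as recorded |
| Can be excluded as non-adherent on these data | yes | no |

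**3. Size of the selection effect (illustration).** Assumptions, none of them in the article:
- no true iCBT effect
- adherence follows a normal propensity with correlation r to outcome
- the most adherent fraction p of the iCBT arm is kept, and all TAU participants are kept

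The 70% value for p borrows the stated 30% iCBT dropout, which is not an adherence figure.

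Spurious difference in SD units = r × φ(z_p) / p, with φ the standard normal density at the cut-off.

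- p = 0.7: 0.348 / 0.7 = 0.497. For r = 0.2 this gives 0.10 SD; for r = 0.3, 0.15 SD.
- p = 0.5: 0.399 / 0.5 = 0.798. For r = 0.2 this gives 0.16 SD; for r = 0.3, 0.24 SD.

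Relative to 0.4: 0.10 / 0.4 = 25% to 0.24 / 0.4 = 60%.

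**4. False-positive rate at p = 0.7.** Assuming equal allocation, 260 / 2 = 130 per arm and 0.7 × 130 = 91 are kept. SE = √(1/91 + 1/130) = 0.137 SD. By normal approximation:

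| r | spurious difference (SD) | two-sided type I error |
|---|---|---|
| 0.1 | 0.05 | 6.5% |
| 0.2 | 0.10 | 11% |
| 0.3 | 0.15 | 19% |
| 0.4 | 0.20 | 31% |
| 0.5 | 0.25 | 44% |

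**5. The adherence-adjusted model.** If adherence is left missing for TAU-only participants, they drop out of the model. If it is coded zero for them (one possible choice), the arm coefficient compares iCBT non-adherers with all TAU participants. With adherence as yes/no and p = 0.7, that difference under no effect is −r × 0.348 / 0.3 = −1.16r, or −0.23 SD at r = 0.2 and −0.35 SD at r = 0.3. The sign is opposite to the per-protocol error, so the two analyses could disagree when iCBT does nothing.

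**6. A contrast that respects randomisation.** The complier-average causal effect is the intention-to-treat difference divided by the proportion using iCBT. With no true effect its numerator is centred on zero, so selection of adherers does not shift it. It does require that allocation affects outcome only through iCBT use.

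**The case against.** The per-protocol set is not defined, and such definitions usually sit in a statistical analysis plan, which is not shown. The comparison of adherers with unselected controls is therefore conditional on the data described. This stands. But a later definition can only use data that were collected, and the article describes none on TAU received.

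A reader might infer that TAU is recorded nowhere and that differences in it could never be detected. The documents do not support that. The article is condensed, the SPIRIT figure is not reproduced in the text at hand, and the nurse has access to clinic files from which TAU could be extracted. The supportable statement is that TAU received is not described as recorded.

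A reader might also infer that unequal TAU biases the main result. It does not. A change in GP visits or prescribing caused by allocation is part of the effect of offering iCBT, and the intention-to-treat contrast includes it validly. What is limited is attribution to the programme itself.

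The magnitude rests wholly on assumed values of r and p. The planned adjustment for baseline covariates could absorb some of the prognostic selection, so r should be read as what remains after it. The per-protocol analysis is also supplementary; 0.4 serves only as a scale, not as a sign that the main comparison is threatened.

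Finally, the complier-average estimate is not free of the same worry: if allocation changes TAU, its exclusion restriction fails. This is correct, and it is a reason to record TAU in both arms.

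**Conclusion.** The point holds in a limited form. The article describes receipt data for iCBT only, lists no assessment of TAU received, and still commits to per-protocol and adherence-adjusted analyses. Built on the data described, both would be asymmetric between arms. For the per-protocol comparison the illustrative error is 0.10–0.24 SD in favour of iCBT, under no true effect, r = 0.2–0.3 and 50–70% of the iCBT arm kept. These are assumptions, and a weaker correlation gives a smaller error. The intention-to-treat analysis is not affected. The matter is worth correcting because the direction of the per-protocol error is predictable and the remedy is cheap, not because the primary conclusion is at risk.

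**What to change.** - **Inference.** State that intention to treat is the sole basis for between-arm inference. Take treatment adherence out of the models that estimate the arm effect; baseline covariates can stay.
- **Per-protocol analysis.** Replace it with a supplementary complier-average causal effect, with randomisation as the instrument and logged iCBT use as the exposure. State that the exclusion restriction requires TAU not to differ by arm. Alternatively, keep the per-protocol analysis but label it exploratory, with no between-arm inference.
- **TAU received.** When blood results are taken from the patient files at weeks 13 and 52, also record for both arms whether the GP appointment was attended, the number of alcohol-related contacts and any alcohol medication prescribed. Report these by arm. This shows whether TAU was alike and helps to check the exclusion restriction.

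**Cost.** The first two changes are to wording and analysis, and use logs already planned. The third needs modest extra file extraction, including for participants who leave no blood test and whose file might otherwise not be opened. It may also need an ethics or consent check. It is still feasible: the article is dated June 2019, with recruitment to December 2019 and study end in December 2020. For participants already followed up, the items can be extracted retrospectively.

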### Statistical analyses and sample size calculations

Baseline participant characteristics stratified by treatment group will be presented. Group differences will be tested using a *t* test for continuous variables and chi-square tests for categorical outcomes. Multiple imputation will be used to replace missing internal values where appropriate. Within-group changes in the primary outcome (alcohol consumption) and secondary outcomes (*ICD-10* criteria, AUDIT scores, depression, anxiety, EQ-5D-5 L and biomarkers) at 12 and 52 weeks will be analyzed according to the intention-to-treat principle, using linear mixed models and Poisson regression where appropriate. The models will further be adjusted for baseline covariates and treatment adherence. Per-protocol analyses will also be presented. All tests will be two-sided and *p* values of less than 0.05 considered statistically significant.

The study is designed to demonstrate statistical superiority. An effect-size of 0.61 has been shown in previous Internet studies on high consumers in the general population [25]. Due to a lack of studies on alcohol-dependent patients, our estimate is based on a more conservative effect-size of 0.4, which requires the estimated sample size of 100 participants in each arm to get a power of 80% and a statistically significance 0.05 when using a *t* test. Given an estimated dropout in iCBT of 30%, 260 participants are included in the study [26].

No interim analyses are planned.

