### Aims and research hypothesis

The overall aim of this project is to study new approaches to improve the identification and treatment of alcohol dependence in PC. Specifically, the aim is to investigate the efficacy of an Internet-based CBT program for alcohol-dependent patients in PC.

The research hypothesis for the project is that:

Internet-based Cognitive Behavioral Treatment (iCBT), when added to treatment as usual (TAU) for alcohol dependence in PC, will reduce alcohol consumption more than TAU only.

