### Study design

This is a multi-center, two-group, parallel, RCT to compare the effects of two 12-week interventions: Internet-based Cognitive Behavioral Treatment (iCBT) plus treatment as usual (TAU) or TAU only, designed to demonstrate statistical superiority. The proposed flow of participants through the trial is shown in Fig. 2. Assessments and biomarkers are completed by all participants at baseline (pre randomization) and post treatment at week 13 and week 52.

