#### Outcome measures

Primary outcome is change in alcohol consumption in mean grams per week and mean number of days with heavy drinking (that is > 4/5 drinks for women and men) the last 30 days from baseline to 12 and 52 weeks post inclusion. A drink contains 12 g of alcohol.

For all secondary outcomes mean change from baseline to 12 and 52 weeks post inclusion applies; hazardous drinking and severity of dependence, health-related quality of life, symptoms of depression and anxiety and difference in biomarker levels of heavy drinking and liver pathology.

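### The outcome models are aimed at within-group change, whereas the hypothesis, the superiority design and the sample size all concern a difference between arms

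*Protocol article*

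**What the plan says.** All references are to the protocol article.

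- **Aims and research hypothesis:** iCBT added to TAU "will reduce alcohol consumption more than TAU only". The abstract states the aim in the same comparative terms.
- **Study design:** a two-group parallel RCT, "designed to demonstrate statistical superiority". The statistical section repeats the superiority objective.
- **Outcome measures:** "Primary outcome is change in alcohol consumption in mean grams per week and mean number of days with heavy drinking", from baseline to 12 and 52 weeks. This defines the variable for each participant. It does not say which comparison is made on it.
- **Statistical analyses and sample size calculations, outcome models:** the sentence takes as its subject "Within-group changes in the primary outcome (alcohol consumption) and secondary outcomes", at 12 and 52 weeks, and says that these "will be analyzed according to the intention-to-treat principle, using linear mixed models and Poisson regression where appropriate". No treatment term, group-by-time term or contrast between arms is named.
- **Same section, group differences:** the text reads "Baseline participant characteristics stratified by treatment group will be presented. Group differences will be tested using a"; the methods it then lists are the chi-square test where data are categorical and the t test where they are continuous.
- **Same section, sample size:** effect size 0.4, 100 per arm, 80% power, significance level 0.05, t test. An estimated 30% dropout in iCBT leads to 260 participants. "All tests will be two-sided".

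**The concern.** Only one sentence links the primary and secondary outcomes to a model, to the follow-up weeks and to intention to treat. The target it gives is change within each group, which is a different quantity from the one in the hypothesis.

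Within-arm change mixes several things. Participants must meet a hazardous-drinking threshold to enter, so some regression to the mean is to be expected. Both arms receive TAU, and the Discussion says that even the control group gets more than it otherwise would. Both arms may therefore improve with no contribution from iCBT. Significant change in both arms says nothing about superiority, and significant change in only one is not evidence that the arms differ.

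At stake is the confirmatory test. Readers will judge the results against the published text, and that text does not identify which model result answers the research question.

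**Working it through.** **1. What the sample size is for.** Inputs from the statistical section: standardised effect d = 0.4, two-sided α = 0.05, power 80%, equal arms.

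Normal approximation: n per arm = 2 × ((1.960 + 0.842) / 0.4)² = 98.1, rounded up to 99.

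Exact two-sample t test: n = 99.08, so 100 per arm, with power 80.4% at 100.

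A one-sided test would need 2 × ((1.645 + 0.842) / 0.4)² = 77.3, so 78 per arm, which does not match. The stated 100 is thus a two-sided comparison between arms.

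**2. The statements side by side.**

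| Element | Quantity it concerns |
|---|---|
| Hypothesis | Difference between arms in reduction |
| Design | Superiority of one arm over the other |
| Sample size | Two-sample t test between arms |
| Mixed and Poisson models | Within-group change |

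The first three agree and the fourth does not. The sentence on group differences does not close the gap. It directly follows the presentation of baseline characteristics and mentions neither the primary outcome, nor weeks 12 or 52, nor the mixed models.

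**3. What would follow if superiority were read from within-arm tests.** The article states no such rule, so this step is conditional. Assume a paired t test in each arm, two-sided α = 0.05, independent arms, and the same true change δ in both arms (in SDs of change), so that iCBT has no effect. Analysed numbers are 100 per arm (the target) and 91 per arm (130 × 0.70).

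Let p be the power of the paired t test, from the non-central t distribution with n − 1 degrees of freedom and non-centrality δ√n. Then P(significant in iCBT, not in TAU) = p(1 − p), and P(both significant) = p².

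| δ (assumed) | p, n = 91 | p(1 − p) | p, n = 100 | p(1 − p) |
|---|---|---|---|---|
| 0.20 | 0.471 | 24.9% | 0.508 | 25.0% |
| 0.25 | 0.655 | 22.6% | 0.697 | 21.1% |
| 0.30 | 0.808 | 15.5% | 0.844 | 13.2% |
| 0.40 | 0.965 | 3.4% | 0.977 | 2.2% |
| 0.50 | 0.997 | 0.3% | 0.999 | 0.1% |

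A between-group test at two-sided 0.05 gives 2.5% in favour of iCBT when there is no effect. At δ = 0.50 both arms are significant with probability 99.4% (n = 91) or 99.7% (n = 100). The false-positive pattern has then almost vanished, but the pair of tests no longer carries information about superiority.

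The article gives no expected within-arm change, so every δ is an assumption.

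**The case against.** The strongest reply is that a comparison is plainly intended. The abstract, the hypothesis, the design statement and the sample size all say so, and intention to treat has little purpose unless randomised arms are compared. A mixed model fitted to both arms could well hold a group-by-time term, and *within-group changes* may be loose wording for change from baseline. This is a fair account of intent, and the defect may be one of wording only. It still leaves the written target of the models at odds with the rest of the article.

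Three stronger readings are tempting, and the text does not support them.

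- *The trial will claim superiority from separate tests in each arm.* No arm-by-arm models are described, and no rule of the kind significant in one arm but not the other is stated. The error rates above are therefore conditional.
- *The comparison has no defined power.* It has: 80% at effect size 0.4 with 100 per arm. What is missing is the link from that contrast to the mixed model.
- *The article contains no sentence on testing between groups.* It contains one, and because it speaks of categorical *outcomes* it could be read more widely than baseline. Its position makes the baseline reading more natural. On the wider reading, the article would hold two unreconciled analyses: t tests between groups and mixed models of within-group change.

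It is also fair that an article may leave to the analysis plan how baseline enters the model and whether within-group p values are shown. Neither is part of this point. The point is a target that the article states, and states wrongly.

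**Conclusion.** The point holds as an internal contradiction. The stated target of the outcome models does not match the hypothesis, the superiority objective or the basis of the sample size. As written, the model analysis does not test the hypothesis for which the trial is powered. This conclusion rests on the text and on the reproduced sample size, and it needs no assumption about the size of change.

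The numerical consequence is conditional on a decision rule that the article does not state and on assumed common changes. Under that rule, the chance of significance in iCBT but not in TAU would be about ten times the 2.5% benchmark at 0.20 SD (25 / 2.5 = 10), close to it at 0.40 SD, and below it at 0.50 SD. It should not be quoted as the trial's error rate.

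**What to change.** In the sentence on the outcome models, replace the opening reference to within-group changes with *Between-group differences in change from baseline in*. Add one sentence: the iCBT+TAU minus TAU contrast from the model (group-by-time), with its 95% confidence interval, is the test of the research hypothesis. Within-group changes may be reported as descriptive. It would also help to say whether the t tests and chi-square tests of group differences concern baseline characteristics only.

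The cost is a few lines of text. The data, the model family, the 100 per arm and the 80% power do not change. The protocol is dated June 2019 and the study is due to conclude in December 2020, so on those dates the correction can be made before the study ends.

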**Methods:**

This is a two-group, parallel, randomized controlled trial (RCT). The aim is to study whether an Internet-based Cognitive Behavioral Treatment (iCBT) when added to treatment as usual (TAU) is more effective than TAU only for alcohol dependence in PC. Two hundred and sixty adults with alcohol dependence will be included. Participants are randomized to iCBT and TAU or TAU only. The primary study outcome is alcohol consumption in grams per week and heavy-drinking days. Secondary outcomes include alcohol-related problem severity, number of diagnostic criteria for alcohol dependence, depression and anxiety symptoms, health-related quality of life and biochemical markers for high consumption and liver pathology. Data will be analyzed using mixed-effect models.

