#### Inclusion criteria

Participants have to meet criteria for alcohol dependence, based on the *International Statistical Classification of Diseases and Related Health Problems – Tenth Revision* (*ICD-10*). Participants also have to meet the threshold for hazardous drinking, which is defined as six or more points for women and eight or more points for men on the Alcohol Use Disorders Identification Test (AUDIT) [20].

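### Poisson regression is the only count model named; if it is used for heavy-drinking days with default standard errors, type I error exceeds 5% once the variance exceeds the mean

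*Protocol article*

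**What the plan says.** The abstract of the protocol article (Methods) states that "The primary study outcome is alcohol consumption in grams per week and heavy-drinking days", and then that "Data will be analyzed using mixed-effect models". Under Outcome measures, the second primary component is the change in "mean number of days with heavy drinking" over "the last 30 days from baseline to 12 and 52 weeks post inclusion". Under Baseline and follow-up assessments, a 30-day Time Line Follow Back "is used to assess mean weekly alcohol consumption and heavy-drinking days". The outcome is therefore a count between 0 and 30, recorded at baseline and twice afterwards.

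Under Statistical analyses and sample size calculations, the primary outcome (described there only as alcohol consumption) and the secondary outcomes are to be analysed "using linear mixed models and Poisson regression where appropriate". "All tests will be two-sided", at the 0.05 level. The section names no other count model. It does not say which outcomes get Poisson, whether a Poisson model would carry random effects, or how its standard errors would be obtained.

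**The concern.** Poisson regression in its default form takes the variance of the count to equal its mean. Drinking days within one person tend to resemble each other, and people with dependence may range after treatment from abstinent to drinking heavily on most days. Either feature makes counts vary more between participants than Poisson allows. Default standard errors are then too small, confidence intervals for the rate ratio too narrow, and p values too low.

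The stake is a primary outcome. A significant difference in heavy-drinking days could then owe more to the variance assumption than to the intervention. The opening phrase of the abstract's Background, which places dependence on a continuum of severity, and an iCBT programme that aims at cutting down or stopping both make wide spread plausible. Neither gives a figure for it.

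**Working it through.** **The plan's own figure.** The article gives 100 per arm for a standardized effect of 0.4, 80% power and two-sided 0.05. Normal approximation: 2 × (1.960 + 0.842)² / 0.4² = 98.1, so 99. The exact t test gives 99.1, and power at 100 per arm is 80.4%. The figure reproduces, and 100 per arm is used below. The article states no mean, variance or dispersion for heavy-drinking days, so everything about spread is assumed and shown as a range.

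**Step 1: size of the default Poisson test.** Let φ = variance/mean. The default standard error is too small by a factor √φ, so type I error = 2 × [1 − Φ(1.96/√φ)].

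| φ | Type I error |
|---|---|
| 0.7 | 1.9% |
| 1 | 5.0% |
| 1.5 | 11.0% |
| 2 | 16.6% |
| 3 | 25.8% |
| 4 | 32.7% |
| 6 | 42.4% |

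**Step 2: what makes φ exceed 1.** For a count out of 30 days with average daily probability p and within-person correlation ρ between days (beta-binomial), φ = (1 − p)(1 + 29ρ).
- With ρ = 0, φ = 1 − p, for example 0.7 at p = 0.3. The 30-day ceiling alone gives less variance than Poisson, so the test is conservative.
- φ passes 1 when ρ exceeds [1/(1 − p) − 1]/29. That is 0.015 at p = 0.3 and 0.034 at p = 0.5.
- At p = 0.3 the mean is 30 × 0.3 = 9 days, and Poisson allows a standard deviation of only √9 = 3 days.
- At p = 0.3 and ρ = 0.05, 0.1, 0.2 and 0.3, φ = 1.72, 2.73, 4.76 and 6.79.

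**Step 3: simulation with no treatment effect** (beta-binomial counts, 100 per arm, 1,000 runs per row; Monte Carlo standard error at 5% is √(0.05 × 0.95/1000) = 0.7 points). For the baseline and two-visit columns, each participant had a 60% chance of keeping the same underlying rate at the other visit.

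| p, ρ | φ | Default, one visit | Default, baseline-adjusted | Default, two visits as independent | Robust, one visit | Cluster-robust, two visits |
|---|---|---|---|---|---|---|
| 0.2, 0.02 | 1.26 | 8.6% | 7.8% | 10.4% | 5.9% | 6.1% |
| 0.3, 0.05 | 1.72 | 12.5% | 10.7% | 19.6% | 4.4% | 5.5% |
| 0.3, 0.1 | 2.73 | 22.6% | 18.0% | 32.1% | 5.7% | 4.9% |
| 0.3, 0.2 | 4.76 | 34.3% | 28.4% | 44.5% | 4.1% | 4.4% |
| 0.3, 0.3 | 6.79 | 42.1% | 36.6% | 54.2% | 5.1% | 5.7% |
| 0.5, 0.3 | 4.85 | 39.3% | 26.4% | 47.9% | 4.8% | 4.7% |

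**Step 4: a random intercept alone.** Random-intercept Poisson, group-by-time term, two visits, p = 0.3, 150 runs per setting:
- every participant's rate stable: 1.3% (ρ = 0.1) and 0.7% (ρ = 0.3);
- 40% of participants drawing a new rate between visits: 12% (ρ = 0.1) and 30% (ρ = 0.3).

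With 150 runs these are rough: the Monte Carlo standard error at 30% is √(0.3 × 0.7/150) = 3.7 points. The direction is clear. The intercept absorbs stable differences between people but not change within them.

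**The case against.** The strongest reply is that the article does not commit to the faulty analysis. It never assigns Poisson to heavy-drinking days. The number of diagnostic criteria is another count to which it could apply, and a change in a mean could be analysed with a linear mixed model. Poisson regression names a model for the mean, and robust or scaled standard errors are not excluded. Overdispersion handling is often settled in an analysis plan, and none is shown here.

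Much of this stands, and it rules out four stronger readings that a reader might infer:
- *Type I error will be above 5%.* This does not follow, because neither the outcome assignment nor the variance estimator is stated. The robust Poisson results in the working show that the mean model does not itself force inflation.
- *Correlation between visits is ignored.* The statistical section attaches the word mixed only to the linear models, but the abstract says "Data will be analyzed using mixed-effect models". A mixed Poisson model is at least as natural a reading.
- *The 30-day bound causes the inflation.* It acts the other way, and heterogeneity between people is needed to overcome it.
- *The documents show overdispersion.* They do not. The entry rule, "Participants have to meet criteria for alcohol dependence", says nothing about the distribution of heavy-drinking days.

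What the reply does not remove is that the article names a specific method. The phrase about appropriateness chooses between two named models and offers no third. Of those two, Poisson is the obvious one for a day count. Its default standard errors fail under modest spread, and reading it as a mixed model does not reliably rescue it.

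**Conclusion.** The point holds conditionally. If heavy-drinking days are analysed by Poisson regression with model-based standard errors, type I error on this primary component exceeds 5% whenever the variance exceeds the mean: 11% at a ratio of 1.5, 17% at 2 and 33% at 4. Adding only a random intercept leaves it anywhere from about 1% to 30%.

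Three things are assumed: that Poisson is meant for this outcome, that its standard errors are not corrected, and that the ratio lies in the range shown. The last is the safest, since a within-person day correlation of about 0.015 at p = 0.3, or 0.034 at p = 0.5, is enough to pass 1. The size of any excess cannot be known from the article. The finding concerns a named method that is unsafe in its default form for this outcome. It does not show that the trial's result will be wrong.

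**What to change.** For heavy-drinking days, replace the general reference to Poisson regression with one of these, each with group, time and group-by-time:
- a Poisson mean model fitted by GEE with participant-clustered robust standard errors; or
- a negative binomial mixed model, or a beta-binomial mixed model out of 30 days.

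Report the between-group ratio with that model's interval: a rate ratio, or an odds ratio for the beta-binomial.

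The simulation supports the first option directly, since clustered Poisson is GEE with an independence working correlation. The mixed models were not simulated. GEE makes a stricter assumption about missing visits than a likelihood-based mixed model. With 30% dropout expected in the iCBT arm, that bears on the choice.

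The cost is one line of text and standard software, with no new data. Intervals will be wider than the default Poisson ones, by about √φ for a single visit: 1.4 times at a ratio of 2 and 2 times at a ratio of 4. The section on randomization and blinding keeps allocation codes from researchers and analysts until the primary analysis is complete, so the choice can be fixed before results by arm are known.
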